## **2.7 Risk/Benefits**

*Please insert a summary of the known and potential risks & benefits, if any, to human subjects*

### **2.7.1 Potential Risks**

#### **2.7.1.1 General risks**

Gardasil does not contain thiomersal preservative. It does not contain live organisms and cannot cause HPV infection or disease. The VLPs contain no viral DNA, they cannot infect cells, reproduce, or cause disease.

Venepuncture may be associated with bruising, localised discomfort and fainting. Dedicated clinical facilities, including phlebotomy chairs will be used and staff must be trained and experienced in venepuncture. The blood volumes drawn over 20 weeks do not present a significant risk of causing anaemia in a healthy person, and subjects must be screened for anaemia before entry.

Vaginal speculum examination can be uncomfortable, and staff must be experienced in the technique. Collection of secretions onto single-use, sterile, soft ophthalmic sponges (developed to collect tears) is painless and risk-free. A dedicated room complete with colposcopy couch, private changing and showering area, must be used to minimise subject discomfort and ensure privacy.

Clinical examination and screening blood tests may disclose medical conditions such as HIV, sexually transmitted disease, cervical cancer. Staff taking consent must be trained in pre-test discussions and the Principal Investigator is an Infectious Diseases clinician who can inform subjects of the diagnoses, answer questions or concerns, and arrange appropriate follow-up with the subject's consent.

#### **2.7.1.2 Intramuscular injection**

The following text is taken from sections 4.8 and 4.9 of the Gardasil SPC (Appendix 3):

The following vaccine-related adverse reactions were observed among recipients of Gardasil at a frequency of at least 1.0% and also at a greater frequency than observed among placebo recipients. They are ranked under headings of frequency using the following convention: [Very Common ( 1/10); Common ( 1/100, <1/10); Uncommon ( 1/1,000, <1/100); Rare ( 1/10,000, <1/1,000); Very Rare (<1/10,000), including isolated reports]

*General disorders and administration site conditions:*

Very common: pyrexia.

Very common: at the injection site: erythema, pain, swelling.

Common: at the injection site: bruising, pruritus.

In addition, in clinical trials adverse reactions that were judged to be vaccine- or placebo-related by the study investigator were observed at frequencies lower than 1%:

*Respiratory, thoracic and mediastinal disorders:*

Very rare: bronchospasm.

*Skin and subcutaneous tissue disorder:*

Rare: urticaria.

Seven cases (0.06%) of urticaria were reported in the Gardasil group and 17 cases (0.18%) were seen in the adjuvant-containing placebo group.

In the clinical studies, subjects in the Safety Population reported any new medical conditions during the follow-up of up to 4 years. Among 11,778 subjects who received Gardasil and 9,686 subjects who received placebo, there were 26 cases of non-specific arthritis/arthropathy reported, 19 in the Gardasil group and 7 in the placebo group.

*Post Marketing Experience*

*Post Marketing adverse events have been spontaneously reported for Gardasil and are not listed above.*

Because these events were reported voluntarily from a population of uncertain size, it is not possible to reliably estimate their frequency or to establish, for all events, a causal relationship to vaccine exposure.

*Blood and lymphatic system disorders:* lymphadenopathy.

*Immune system disorders:* hypersensitivity reactions including anaphylactic/anaphylactoid reactions.

*Nervous system disorders:* Guillain-Barré syndrome, dizziness, headache, syncope.

*Gastrointestinal disorders:* nausea, vomiting.

*Musculoskeletal and connective tissue disorders:* arthralgia, myalgia.

*General disorder and administration site conditions:* asthenia, fatigue, malaise

#### **Overdose**

There have been reports of administration of higher than recommended doses of Gardasil. In general, the adverse event profile reported with overdose was comparable to recommended single doses of Gardasil.

#### **Anaphylaxis**

Staff administering challenge agents must be trained in resuscitation and management of anaphylaxis, with regular refreshers. The clinical site will maintain a crash trolley, oxygen, defibrillator and SOPs to manage acute medical emergencies associated with immunisation, including access to emergency services. Adequate numbers of trained staff must be present during challenges.

#### **2.7.1.3 Topical sublingual application**

The risk profile associated with topical sublingual application has not been specifically evaluated, but is expected to be considerably less than after injection given the low level of protein expected to passively cross the oral mucosa, compared with the dose delivered intramuscularly. Single-dose and repeated-dose toxicity and local tolerance studies revealed no special hazards to humans (Gardasil SPC section 5.3 Appendix 3). Natural infection with HPV (which can also be oral) is initially asymptomatic and not associated with localised reactions to L1 proteins on the viral surface that contact the mucosal surface (warts develop after 3 weeks due to the effects on cell growth of internal viral proteins and cancer-promoting genes - not present in the Gardasil preparation).

The tiny (microgram) amounts of L1 protein and alum present no credible risk if swallowed, when compared with the huge (gram) amounts of protein (and other particulates such as toothpaste) swallowed daily. Any swallowed L1 or alum is expected to be immediately degraded by gastric acid and digestive enzymes.

As daily sublingual application of allergens over many months has been shown to be required to induce tolerance to allergic responses, no tolerising effect is expected from the three application of these virus-derived protein antigens at 0, 1 and 4 months proposed here.

#### **2.7.2 Potential Benefits**

By better understanding the common mucosal immune system we will learn more about how the body handles pathogen antigens presented via systemic or mucosa-associated lymph nodes. This may advance our understanding of immune responses to viral infections, and inform the design of mucosal vaccine delivery systems. We will also develop novel assays, and a model of mucosal immune challenge with model viral antigens.

Each subject screened will receive a free basic medical health check.

##### **2.7.2.1 Intramuscular injection**

Section 5.1 of the Gardasil SPC (Appendix 3) details the level of benefit associated with intramuscular immunisation.

In clinical studies, 99.9%, 99.8%, 99.8%, and 99.6% of individuals who received Gardasil became anti-HPV 6, anti-HPV 11, anti-HPV 16, and anti-HPV 18-seropositive, respectively,

by 1 month Post-dose 3 across all age groups tested. Gardasil induced high anti-HPV Geometric Mean Titres (GMTs) 1 month Post-dose 3 in all age groups tested. This level of immunity was associated with high levels (100%) of protection against cervical cancer lesions. Subjects over 18 are not eligible for the free NHS mass immunisation programme and so will benefit from a free vaccination (currently approximately £120 per injection).

Subjects already infected with HPV can expect to gain no benefit against the serotype with which they are infected, but will be protected against other serotypes. Although we will use an alternative schedule of immunisation, it is one recommended by the Gardasil SPC and subjects can expect to receive a high level of benefit in protection against HPV infection and associated cervical cancer or genital warts.

#### **2.7.2.2 Topical sublingual administration**

No data is available for the level of immunity induced by sublingual immunisation. However, due to physical barriers limiting antigen penetration across the oral mucosa, and destruction of swallowed antigen by gastric acid and digestive enzymes, it is expected that any immune responses induced will be low level and non-protective.

It is theoretically possible that topical sublingual exposure may prime subjects for an enhanced immune response to subsequent intramuscular injection, however this is speculative. Subjects should therefore not expect to gain any benefit from inclusion in this arm of the study.

### **2.8 Subject population(s) for analysis**

*Please insert the number of subjects planned to be enrolled. In multi-centre studies, the number of enrolled subjects projected for each study site should be specified. Provide a reason for choice of sample size, including reflection on (or calculations of) the power of the study and clinical justification*

All subjects will be recruited at one site.

We will recruit a total of 18 healthy female volunteers, aged 18-35.

From previous experience we expect the median age to be around 23 years old.

We expect around half the subjects to be naive for the challenge agents, while the remainder will have had some exposure to one or more of the antigens.

We will initially recruit the first SIX subjects into a group that will receive INTRAMUSCULAR challenge.

We will subsequently recruit a further TWELVE subjects into the group to receive SUBLINGUAL challenge.

The numbers have been selected according to our previous experience with mucosal antigen delivery, and the expected circa 100% response rate seen with intramuscular immunisation with HPV vaccines. As this is a hypothesis generating study it is not powered to enable between-group subgroup analysis. A response after challenge in any of the assays will constitute a valid response to challenge. In addition to providing data on antigen handling via systemic or mucosal routes, this study will generate data on the feasibility of sublingual challenge studies, and guide the choice of suitable assays to characterise immune responses in subsequent larger studies.

## 2.9 Study design/type

Please insert a description of the type/design of the study to be conducted (e.g. double-blind placebo controlled, parallel design) and a schematic diagram of the study design, all procedures and stages.

- **Physiology study using a challenge agent, not a CTIMP**
- **Open label, non-randomised, hypothesis generating study**

### 2.9.1 Schedule of visits and procedures

| Visit no.                                                                        | 1         | 2  | 3  | 4  | 5  | 6  | 7   | 8   | 9   |
|----------------------------------------------------------------------------------|-----------|----|----|----|----|----|-----|-----|-----|
| Study day no.                                                                    | -28 to -2 | 0  | 7  | 28 | 35 | 56 | 112 | 119 | 140 |
| Study week no.                                                                   |           | 0  | 1  | 4  | 5  | 8  | 16  | 17  | 20  |
| Study month no.                                                                  |           | 0  |    | 1  |    | 2  | 4   |     | 5   |
| Informed consent                                                                 | X         |    |    |    |    |    |     |     |     |
| In/exclusion criteria                                                            | X         | X  |    | X  |    |    | X   |     |     |
| Demography                                                                       | X         |    |    |    |    |    |     |     |     |
| Pulse, temperature                                                               | X         | X  |    | X  |    |    | X   |     |     |
| Heart (including blood pressure), lungs, abdomen, oral cavity; cervical speculum | X         |    |    |    |    |    |     |     |     |
| Pregnancy test                                                                   |           |    |    |    |    |    |     |     |     |
| Blood                                                                            | X         |    |    |    |    |    |     |     |     |
| Urine                                                                            |           | X  |    | X  |    |    | X   |     |     |
| Urinalysis (dipstick)                                                            | X         |    |    |    |    |    |     |     |     |
| Blood for exclusions (15 mL): FBC, HBV sAg, HIV1&2 Ab, HCV Ab*                   | X         |    |    |    |    |    |     |     |     |
| Challenge                                                                 |           |    |    |    |    |    |     |     |     |
| Group 1: 0.5 mL Gardasil IM                                                      |           | X  |    | X  |    |    | X   |     |     |
| Group 2: 0.5 mL Gardasil sublingual                                              |           | X  |    | X  |    |    | X   |     |     |
| Blood for B / T cell analysis (20-50 mL)†                                        |           | BT | B  | TB | B  | TB | BT  | B   | TB  |
| Blood for serum antibody (5 mL)                                                  |           | X  | X  | X  | X  | X  | X   | X   | X   |
| Cervico-vaginal secretions for antibody                                          |           | X  |    | X  |    | X  | X   |     | X   |
| Volume of blood drawn (Total: 380 mL)                                            | 15        | 55 | 25 | 55 | 25 | 55 | 55  | 25  | 55  |

\* FBC: Full Blood Count. HBV sAg: Hepatitis B virus surface antigen. HIV1&2 Ab: Antibody for HIV1 & 2 viruses. HCV Ab: Antibody to Hepatitis C virus

† 50 mL total split as 15 mL to B cell assay / 35 mL to T cell assay on days when both taken. Otherwise 20 mL for B cell assays and 50 mL for T cell assays on days when taken alone

### 2.9.2 Acceptable Visit Windows

Visits within the following window periods will not constitute a protocol deviation:

Visits 3, 5 and 8: +/- 1 day

Visits 4, 6, 7 and 9: +/- 2 days

Given the exploratory nature of this study, it will be acceptable to collect and analyze samples taken at the *closest possible time* to the scheduled visit, if the subject is unable to make the scheduled visit. No additional visits are allowed.

### 2.9.3 Details of study visits

The length of visits will vary according to the purpose of each particular visit.

After initial contact expressing interest in the study, subjects will receive verbal information and an Information Sheet which they are encouraged to discuss this with their GP, friends and family. After at least 24 hours subjects will be eligible to sign written consent, having had a pre-test discussion relating to HIV testing. They are then eligible to make Visit 1.

#### **Visit 1: Eligibility check**

(Between 28 and 2 days before visit 2)

Basic demographic information will be collected to identify subject, and to check inclusion/exclusion criteria. No information relating to race, height, weight will be collected. Past and current medical and medication history will be recorded to check exclusion criteria. A general medical examination (heart, lungs, abdomen, mouth, vagina-cervix (with speculum) will be performed. Pulse and temperature recorded.

Blood will be taken and tested for Full Blood Count, HIV and Hepatitis B and C infections, pregnancy. Urine dipstick analysis.

#### **Visits 2, 4 and 7: Antigen delivery and immunology response follow-up**

(Day 0, 28 and 112)

Pulse and temperature recorded. General state of health, concomitant medications elicited to determine any exclusion/withdrawal criteria. Urine pregnancy test carried out.

Blood taken for immunology assays:

- Serum on all visits
- B cell assays visits 2 & 7
- T cell assays on all visits

Vaginal-cervical secretions collected onto a soft ophthalmic sponge using a speculum, for immunology assays.

The HPV antigens are given sublingually (as drops placed onto the undersurface of the tongue) or by injection (into the upper arm muscle) - according to study group.

#### **Visits 3, 5, 6 and 8: Immunology response follow-up**

(Day 7, 35, 56, 119)

Blood taken for immunology assays:

- Serum on all visits
- B cell assays visits 3, 5 & 8
- T cell assays visit 6

Vaginal-cervical secretions collected onto a soft ophthalmic sponge using a speculum at visit 6, for immunology assays

#### **Visit 9: Final immunology response follow-up**

(Day 140)

At the final visit blood will be taken for T cell and serum immunology assays. Vaginal-cervical secretions collected onto a soft ophthalmic sponge using a speculum, for immunology assays.

On **one only** of visits 2, 4, 6, 7 **or** 9 subjects will be invited to collect a vaginal sample using the self-inserted and self-removed 'Instead cup' in addition to weck-cel samples. Participation in this procedure is voluntary and not required for protocol compliance. This sample may be used for immunology assays or by collaborators investigating the *in vitro* effects of healthy cervico-vaginal samples on vaccine antigen integrity. Samples will be processed according to laboratory SOPs of the collaborating laboratories.

This concludes a subject's participation.

Protocol 04-02c

## **2.10 Data Identification**

*Please insert the identification of any data to be recorded directly on the Case Report Forms (CRFs) (i.e. no prior written or electronic record of data), and to be considered to be source data*

Source data will consist of the subject demographics, results of screening exclusion assays, physical examination, administration of challenge agents, details of vials used, allocation to group, and will be entered directly onto the CRFs.

Results of immunological assays will be entered onto paper worksheets, which will be considered source data. Electronic data will be used for subsequent analysis.

## **2.11 Primary and/or Secondary Study Endpoints**

*Please insert a specific statement of the primary endpoints and the secondary endpoints, if any, to be measured during the study*

No primary and secondary endpoints are defined in this hypothesis-generating study.

A number of exploratory variables will be measured:

1. Concentration, neutralising activity and isotype profile of antigen-specific antibody in serum and cervico-vaginal secretions measured by ELISA and/or LUMINEX assay and virus neutralisation assay
2. Frequency and isotype profile of antigen-specific antibody secreting cells in blood measured by ELISPOT assay
3. Frequency and expression profile of mucosa-associated homing, memory and regulatory markers on antigen-specific T cells in blood in response to *in vitro* antigen stimulation measured by Flow Cytometry (FACS) and CFSE proliferation assay
4. Profile of cytokine secretion by peripheral blood mononuclear cells in response to *in vitro* antigen stimulation measured by ELISA

## **2.12 Randomisation**

*Please insert a description of the measures taken to minimize/avoid bias, including randomisation (please include a description of the method) and blinding (if applicable)*

There will be no randomisation.

The nature of the challenge makes blinding impossible and no placebo or comparator will be used. Each subject acts as their own control, comparing pre-challenge with post-challenge time points.

The first 6 subjects will be recruited into the intramuscular challenge group, to allow assays to be developed and positive control samples generated, as this route of challenge is known to reliably induce mucosal and systemic immune responses.

The remaining 12 subjects will then be entered into the sublingual group.

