| Challenge Agents       | 
Purified, recombinant L1 protein antigens from Human Papilloma Virus serotypes 6, 11, 16 & 18 in the following amounts:
 
Human Papillomavirus Type 6 L1 protein 20 micrograms
 Human Papillomavirus Type 11 L1 protein 40 micrograms
 Human Papillomavirus Type 16 L1 protein 40 micrograms
 Human Papillomavirus Type 18 L1 protein 20 micrograms
 
adsorbed on amorphous aluminium hydroxyphosphate sulphate adjuvant (225 micrograms Al)
                                                                                                                                                                                                                                                                              |
| Study design           | 
 
• Physiology study using challenge agents, non-CTIMP
 
• Open label, non-randomised, hypothesis generating study
 
                                                                                                                                                                                                                                                                                                                                                                                                                                                                                                                                                                                  |
| Sample size            | 
EIGHTEEN subjects in all, in two groups:
 
(1) SIX receiving challenge agents by intramuscular injection of deltoid muscle
 
(2) TWELVE receiving challenge agents sublingually
                                                                                                                                                                                                                                                                                                                                                                                                                                                                                                                                                           |

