| Route of Administration           | 
 
1. Intramuscular (deltoid injection): 6 subjects
 
2. Sublingual (as drops under the tongue): 12 subjects
 
 
Given on three occasions at 0, 1 and 4 months
                                                                                                                                                                                                                                                                                                                                                                                                                                                                                                                                                                                 |
| Duration of Treatment             | 
The entire duration of the study will be 20 weeks (up to 24 weeks including screening period).
 
During this period subjects will make a total of 9 outpatient visits to the clinical site
                                                                                                                                                                                                                                                                                                                                                                                                                                                                                                                                                                                                  |
| Primary & Secondary endpoints | 
No primary and secondary endpoints are defined in this hypothesis-generating study.
 
A number of exploratory variables will be measured.
                                                                                                                                                                                                                                                                                                                                                                                                                                                                                                                                                                                                                                                   |

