8. The "Gardasil" preparation has the advantage of containing 4 different L1 antigens (from strains 6, 11, 16 and 18). Seroepidemiology of women aged 23 (the median age of subjects generally recruited into our studies) in England shows that around 45% already have immunity to at least one of the 4 antigens, but only 15% have immunity to two or more. This means that in our sample we will expect half the subjects not to be immune to any of the antigens, in whom we can study priming and boosting responses to a neoantigen, which is the most interesting aspect of this study - as previous genital tract infection may bias the subsequent response to the sublingual immune challenge.

However, we will also have around half of the subjects in whom we can simultaneously study responses to recall antigens that they have seen before (thereby increasing our prospects of seeing any response at all to sublingual challenge) and neoantigens. While this hypothesis generating study is not powered to analyse subgroup responses to the 4 antigens in detail, by determining subject's serostatus at entry it will be interesting to see if there is any suggestion that prior genital tract infection modulates the response to

cross-reacting antigens. Prior genital infection is essentially a mucosal immunological prime, which may be boosted by the mucosal (sublingual) or parenteral (intramuscular) boost in different ways. It has recently been shown that around 1% of young women have oral infection with HPV, which might theoretically modulate the immune response. However the low prevalence is unlikely to significantly affect the number of subjects being studied. Any observed differences in immune responses between subjects seropositive or seronegative at entry could be further investigated in larger studies.

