## 2.5 Population

*Please insert a description of the population to be studied (including sample size, participant group, patient group (if applicable)). Please indicate if a vulnerable population is to be studied*

- We will recruit a total of 18 healthy female volunteers, aged 18-35.
- All subjects will be healthy, and will provide written informed consent.
- No vulnerable groups will be included.
- From previous experience we expect the median age to be around 23 years old.
- We expect around half the subjects to be naive for the challenge agents, while the remainder will have had some exposure to one or more of the antigens.

As group size is small in this hypothesis generating study we have elected to recruit a narrow age range, to avoid possible bias due to age-related (hormonal) changes in immune response, especially in the genital tract.

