### **2.30 Statistical methods**

*Please insert a description of the statistical methods to be employed including timing of any planned interim analysis(es), level of significance to be used*

No primary and secondary endpoints are defined in this hypothesis-generating study.

A number of exploratory variables will be measured. As this is a hypothesis generating study it is not powered to enable between-group subgroup analysis. A response after challenge in any of the assays will constitute a valid response to challenge.

Appropriate statistical tests of significance (parametric or non-parametric) will be used for between-group, or between-time-point analyses of exploratory variables, according to the nature and size of the dataset, and in consultation with a statistician before publication.

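### With only a before/after control, the any-assay rule would credit a natural HPV seroconversion during the 140 days to the sublingual challenge

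*Protocol*

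**What the plan says.** Section 2.12 rules out randomisation and blinding and states that "no placebo or comparator will be used". The control is within the subject: "Each subject acts as their own control, comparing pre-challenge with post-challenge time points". The intramuscular group receives the same antigens as a positive reference, so it cannot show how often antibody rises without a challenge.

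Section 2.30, repeating 2.8, says: "A response after challenge in any of the assays will constitute a valid response to challenge". Neither section attaches a condition on the number of HPV types, on the type's serostatus at entry or on timing after a challenge.

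The Synopsis has "TWELVE receiving challenge agents sublingually", and the schedule in 2.9.1 follows them from day 0 to day 140. Section 2.1 (item 8) says of women aged 23, the expected median age, that "around 45% already have immunity to at least one of the 4 antigens, but only 15% have immunity to two or more". It plans to determine serostatus at entry and mentions oral infection at around 1%. It does not mention infection acquired after entry. The schedule has no HPV infection test at any visit, and 2.15 does not exclude HPV infection as such. For the sublingual route, 2.7.2.2 says "it is expected that any immune responses induced will be low level and non-protective".

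**The concern.** A before/after comparison attributes a change correctly only if little besides the challenge can move the marker. Here something else can: a woman who seroconverts to one HPV type from natural infection during the 20 weeks shows a real rise in L1 antibody after challenge. Under the any-assay rule she is a responder.

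The error runs in one direction and affects one group. Intramuscular response is expected at about 100% (2.8), so that count has almost no room to rise. Sublingual responses are expected to be lower and less frequent (2.1), so a single misattributed subject can turn no response into a response. Section 2.8 wants the study to inform the feasibility of sublingual challenge and the choice of assays for larger studies, and that is where a misread responder would do harm.

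**Working it through.** The protocol states no incidence, power or responder rate, so there is no figure of its own to reproduce. Its serology is consistent with its text: 45% seropositive leaves 55% naive, in line with its expectation of about half, or 12 × 0.55 = 6.6 sublingual subjects.

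**Inputs from the protocol.** 12 sublingual subjects; 140 days = 140/365.25 = 0.383 years; 45% immune to at least one type and 15% to two or more, hence 45 − 15 = 30% to exactly one.

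**Assumptions.** Years at risk before age 23, Y = 7 (range 5 to 9); a constant hazard; two or three types in a woman immune to more than one; types independent.

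**A. All susceptible types in all 12 subjects.**

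- Mean prevalence per type: q = (0.30 + 0.15 × k)/4, which is 0.150 for k = 2 and 0.1875 for k = 3.
- Hazard per type: −ln(1 − q)/Y. At Y = 7 this is 0.0232 to 0.0297 per year.
- Risk per susceptible type over 140 days: 1 − exp(−hazard × 0.383) = 0.89% to 1.13%.
- Susceptible subject-types: 12 × 4 × (1 − q) = 40.8 or 39.0.
- Expected new seroconversions, m = 40.8 × 0.00886 = 0.36, or 39.0 × 0.01131 = 0.44.
- Chance of at least one: 1 − exp(−m) = 30% to 36%.

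The extremes are Y = 9 with k = 2 (m = 0.28, 25%) and Y = 5 with k = 3 (m = 0.62, 46%). The chance of two or more, 1 − exp(−m)(1 + m), is 3% and 13% at these extremes.

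**B. First seroconversion in fully naive subjects only.**

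- Hazard: −ln(0.55)/Y = 0.085 per year at Y = 7 (0.120 at 5, 0.066 at 9).
- Risk over 140 days: p = 3.2% (4.5%, 2.5%).
- Chance of at least one among 6.6: 1 − (1 − p)^6.6 = 19% (26%, 15%).

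B leaves out women already immune to one type who acquire another, so it is the narrower count.

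**Effect on the result.** One such subject turns 0/12 into 1/12 (8%, exact 95% interval 0.2% to 38%).

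**What could separate the two sources.** Every challenge contains all four types, whereas 30/45 = two thirds of naturally immune women are immune to one type only. B-cell blood is already scheduled on days 7, 35 and 119, each 7 days after a challenge.

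**The case against.** **The size rests on unseen inputs.** Prevalence at one age is not incidence, and continuing exposure is inferred, not stated. This stands. The figures are a range under assumptions; if the true 20-week risk were 1% per subject, the chance of at least one in 12 would be 1 − 0.99^12 = 11%.

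**Removing every one-type rise would work against the design.** Section 2.1 includes previously exposed women because a recall response improves the prospect of seeing anything after sublingual challenge. About 0.30 × 12 = 3.6 sublingual subjects should be immune to exactly one type, and a boost to that type may be their likeliest true response. Losing those to remove about 0.4 false ones would be a poor exchange. This stands, so a recall rise should stay in the count.

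**The discriminators are imperfect.** One third of naturally immune women (15 of 45) have two or more types, and 2.1 itself allows that antigens cross-react. Section 2.3 warns that not every assay will work in every subject, and the antibody-secreting-cell assay is not among its core assays. This also stands, and is why unclear cases should be labelled and not deleted.

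**Responder definitions belong in the analysis plan.** This is partly right: size of rise and per-type cut-offs may be set there. The protocol itself, however, states that a response in any assay is a response to challenge.

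**Nothing formal depends on 0/12 versus 1/12.** True: there are no primary or secondary endpoints and no success threshold. This limits the consequence, but a wrongly attributed responder could still seed the wrong hypothesis.

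A reader might also infer that no stricter cut-off or second baseline could help, because a natural rise is real antibody. The documents do not support that: they give no size for natural rises, and a second baseline might reveal titres already rising before day 0.

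**Conclusion.** The concern holds in limited form. The attribution rule in 2.8 and 2.30, combined with a before/after control, cannot tell a natural one-type seroconversion from a sublingual response. On a constant hazard and 5 to 9 assumed years at risk, about 0.3 to 0.6 such events are expected among the 12 sublingual subjects. The chance of at least one is roughly 25% to 46%, or 15% to 26% counting fully naive subjects only.

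A reader might infer that sublingual responses in this study would be uninterpretable. The figures do not support that. Natural infection could explain one apparent responder, rarely two; it could not explain a response in most subjects, and the intramuscular findings are hardly affected. The change is worth making because it is cheap and because the sublingual signal is expected to be small.

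**What to change.** In 2.8 and 2.30, classify each antibody rise by HPV type and by entry serostatus for that type, which 2.1 already plans to determine. Attribute a rise to the challenge if it is:

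- in two or more types at the same visit;
- in one type that was already seropositive at entry, labelled as a recall response; or
- in one type, matched by antibody-secreting cells for that type at the visit 7 days after a challenge (visit 3, 5 or 8).

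Label a one-type rise in a type seronegative at entry, with antibody-secreting cells absent or not measured, as 'challenge or natural infection'. Report the number of sublingual responders with and without these subjects.

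The cost is a short paragraph and one table row, with no new visit or sample; the cell criterion needs results by type. A true one-type primary response without cell data is marked uncertain, though still reported. Some natural events still pass: an infection that raises two or more types at once, and a reinfection that boosts a type already seropositive at entry.
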